## Analysis plan

|                                                                                              |                                                     |                                                  |                                        |                                                |                                          |                                                                                                                                                                                                                                                                                  |
|----------------------------------------------------------------------------------------------|-----------------------------------------------------|--------------------------------------------------|----------------------------------------|------------------------------------------------|------------------------------------------|----------------------------------------------------------------------------------------------------------------------------------------------------------------------------------------------------------------------------------------------------------------------------------|
|                                                                                              |                                                     |                                                  |                                        |                                                |                                          | 
 
• Missing if afsp1e has any other value
 
                                                                                                                                                                                        |
| Partnership status (married/cohabiting vs. single)                                           |                                                     |                                                  |                                        |                                                |                                          | Based on algorithm defined by Statistics Denmark. Those who have non-missing data on variables EFALLE (table BEF, during 1986-) and C_faelle_id (table FAIN, 1980-1985) will be recorded as in a partnership (=1) and remaining patients are considered single (=0) b |
| Gross personal income                                                                        |                                                     |                                                  |                                        |                                                |                                          | Based on variable PERINDKIALT_13 (during 1987-) and PERINDKIALT (1980-1986). Categorized yearly (to account for inflation) based on quartiles.                                                                                                                                   |
| Immunosuppression (immunosuppressive disorders and drugs, excluding oral corticosteroid use) | "07983"
"28401"
"28402"
"28408"
"28409" | "DB20"
"DB22"
"DB24"
"DZ21"
"DZ948C" | "DB21"
"DB23"
"DF024"
"DT860" | Procedure codes:
"BOQE"
"BOQF"
"BOHJ" | "L01"
"L04"
"V02CA01"
"V02CA02" | Exclude codes for myeloma, lymphoma and leukemia respectively from code list for the                                                                                                                                                                                             |

|         |                        |             |                   |
|---------|------------------------|-------------|-------------------|
| "75830" | "DZ948" (if not        | "BWG"       | variable when     |
| "203"   | "DZ948A"               | "BWHB"      | these cancers are |
| "204"   | "DZ948B" or            |             | the outcome       |
| "205"   | "DZ948C" and if | Or          | (ICD-8: "203"     |
| "206"   | coded as a B-          |             | "204" "205"       |
| "207"   | diagnosis or           | Any ATC     | "206" "207"       |
| "200"   | additional             | code for    | "200" "201"       |
| "201"   | diagnosis together     | "L01"       | "202"; ICD-10:    |
| "202"   | with one of the        | "L04"       | "DC90" "DC91"     |
|         | following A-           | "V02CA0     | "DC92" "DC93"     |
|         | diagnoses              | 1" or       | "DC94" "DC95"     |
|         | "DC770" "DC81"         | "V02CA0     | "DC81" "DC82"     |
|         | "DC82" "DC83"          | 2" used as  | "DC83" "DC84"     |
|         | "DC84" "DC85"          | additional  | "DC85" "DC86"     |
|         | "DC86" "DC87"          | code in the | "DC88"            |
|         | "DC88" "DC89"          | Patient     | "DC96")           |
|         | "DC90" "DC91"          | Registry    |                   |
|         | "DC92" "DC93"          |             |                   |
|         | "DC94" "DC95"          |             |                   |
|         | "DC96", "DD45"         |             |                   |
|         | "DD46" "DD47"          |             |                   |
|         | "DD5" "DD6"            |             |                   |
|         | "DD7"                  |             |                   |
|         | "DD80" "DD81"          |             |                   |
|         | "DD82" "DD83"          |             |                   |
|         | "DD84" "DD85"          |             |                   |
|         | "DD87" "DD88"          |             |                   |
|         | "DD89" "DT860"         |             |                   |
|         | "DT860A"               |             |                   |
|         | "DT888N")              |             |                   |
|         | "DD611"                |             |                   |
|         | "DD612"                |             |                   |
|         | "DD613"                |             |                   |
|         | "DD618"                |             |                   |
|         | "DD619" "DD81"         |             |                   |
|         | "DD820"                |             |                   |
|         | "DD821"                |             |                   |
|         | "DD821A"               |             |                   |
|         | "DD822" "DD83"         |             |                   |
|         | "DC90" "DC91"          |             |                   |
|         | "DC92" "DC93"          |             |                   |

|                                                                                                    |                  |                                                                                             |                                        |
|----------------------------------------------------------------------------------------------------|------------------|---------------------------------------------------------------------------------------------|----------------------------------------|
|                                                                                                    |                  | "DC94" "DC95"
"DC81" "DC82"
"DC83" "DC84"
"DC85" "DC86"
"DC88" "DC96"           |                                        |
| Use of oral corticosteroids                                                                        |                  | "H02AB" and
DOSFOR M "TAB"
or
"TABMO D"                                            | Any prescription excluding injections. |
| Systemic treatment for eczema (cyclosporine, azathioprine, mycophenolate, methotrexate, dupilumab) | Procedure codes: | "L04AX0 1"
"BOHJ18 B8"
"BWHB83 3"
"BWAH1 15"
"BOHJ20"
"BOHJ22"
"D11AH0 5" |                                        |
| Asthma                                                                                             | "493"            | "DJ45" "DJ46"                                                                               |                                        |

Note: All subcodes are included unless otherwise stated; all types of contacts (inpatient, outpatient and emergency) and both primary and secondary diagnoses should be considered. Use admission/prescription/record date for all variables.

aBaseline information only

bDocumentation is available here:

<https://www.dst.dk/da/Statistik/dokumentation/Times/forskningsservice/efalle>

<https://www.dst.dk/da/Statistik/dokumentation/Times/cpr-oplysninger/c-faelle-id>

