### *Exposure subgroups*

For the secondary aim, we will identify severe and active eczema. The analyses will be performed if feasible in terms of sample size.

We will categorize severity as moderate or severe. Severe eczema will be defined as (1) either phototherapy or systemic treatment for eczema (cyclosporine, azathioprine, mycophenolate, methotrexate, dupilumab), identified in Patient Registry (procedure codes: “BNGA1” “BNGA2” “BNGA3” “BNGA4” “BOHJ18B8” “BWHB83” “BWHA115” “BOHJ20” “BOHJ22”) or Prescription Registry (ATC codes: “L04AX01” “L01BA01” “L04AX03” “L04AD01” “L04AA06” “D11AH05”) or (2) admission to hospital with eczema as the primary reason for admission (i.e. where eczema is recorded in the primary diagnostic position for an in-hospital contact). Severity will be included as a time-updated variable. Thus, a patient with eczema will be classified as having moderate eczema from index date (unless they develop severe eczema). When (and if) a person fulfills the definition for severe eczema, we will classify them as having severe eczema from the

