### Sensitivity analyses

8. We will examine if the association is reduced by adjustment for time-varying systemic treatment for eczema. The study is likely insufficiently powered to examine for effect measure modification by immunosuppressive treatments.

**Table 8. Number of events, accumulated person-time, and HRs for cancer associated with eczema, Denmark. Adjusting additionally for systemic treatment for eczema.**

|                          | N | events | P-Y
at
risk | Rate
per
1,000 | Hazard ratio and 99%
confidence interval  |                    |
|--------------------------|---|--------|-------------------|----------------------|----------------------------------------------------------|--------------------|
|                          |   |        |                   |                      | Unadjusted                                               | Mediation
model |
| Any cancer               |   |        |                   |                      |                                                          |                    |
| Unexposed                |   |        |                   |                      |                                                          |                    |
| Exposed                  |   |        |                   |                      |                                                          |                    |
| Lung cancer              |   |        |                   |                      |                                                          |                    |
| Unexposed                |   |        |                   |                      |                                                          |                    |
| Exposed                  |   |        |                   |                      |                                                          |                    |
| Breast cancer            |   |        |                   |                      |                                                          |                    |
| Unexposed                |   |        |                   |                      |                                                          |                    |
| Exposed                  |   |        |                   |                      |                                                          |                    |

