 Unexposed  
 Exposed  
 Leukemia  
 Unexposed  
 Exposed  
 Meningioma  
 Unexposed  
 Exposed  
 Cancer of the brain, hypophysis,  
 corpus pineale and ductus  
 craniopharyngealis  
 Unexposed  
 Exposed  
 Spinal cord, cranial nerve and  
 other CNS tumours  
 Unexposed  
 Exposed

---

Estimated hazard ratios from Cox regression with time since index date as underlying timescale, stratified by matched set.

Unadjusted: No adjustment.

Mediation model: Adjusted additionally for time-varying lifestyle-related diseases.

10. We will repeat the main analysis additionally adjusting for immunosuppression (immunosuppressive disorders or drugs).

---

**Table 10. Number of events, accumulated person-time, and HRs for cancer associated with eczema, Denmark. Adjusting additionally for immunosuppression.**

---

|                 | N | events | P-Y
at
risk | Rate
per
1,000 | Hazard ratio and 99%
confidence interval  |                    |
|-----------------|---|--------|-------------------|----------------------|----------------------------------------------------------|--------------------|
|                 |   |        |                   |                      | ‘Unadjusted’                                             | Mediation
model |
| Any cancer      |   |        |                   |                      |                                                          |                    |
| Unexposed       |   |        |                   |                      |                                                          |                    |
| Exposed         |   |        |                   |                      |                                                          |                    |
| Lung cancer     |   |        |                   |                      |                                                          |                    |
| Unexposed       |   |        |                   |                      |                                                          |                    |
| Exposed         |   |        |                   |                      |                                                          |                    |
| Breast cancer   |   |        |                   |                      |                                                          |                    |

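### Item 10 adjusts for immunosuppressive disorders and drugs through one shared ever/never term that contains most of the systemic eczema drugs in item 8, so a change in Table 10 cannot be attributed on its own

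*Protocol*

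**What the plan says.** Table 3 under Covariables defines the covariate as "Immunosuppression (immunosuppressive disorders and drugs, excluding oral corticosteroid use". The row joins three kinds of code:

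- ICD-8 and ICD-10 disorder codes, including lymphoma, myeloma and leukaemia;
- procedure stems BOQE, BOQF, BOHJ, BWG and BWHB;
- ATC stems L01 and L04, plus V02CA01 and V02CA02.

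The note to the table says "Note: All subcodes are included unless otherwise stated". Under Covariables, a time-updated variable of this kind switches from unexposed to exposed at the first qualifying record and stays there.

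Item 10 reads "We will repeat the main analysis additionally adjusting for immunosuppression (immunosuppressive disorders or drugs". Item 8 has its own covariate, "Systemic treatment for eczema (cyclosporine, azathioprine, mycophenolate, methotrexate, dupilumab", and its own purpose: "We will examine if the association is reduced by adjustment for time-varying systemic treatment for eczema". Under Exposure subgroups the same treatments help to define severe eczema: "either phototherapy or systemic treatment for eczema (cyclosporine, azathioprine, mycophenolate, methotrexate, dupilumab".

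Two rules take codes out of the immunosuppression row. Oral corticosteroids are left to item 11, and the haematological cancer codes are dropped when those cancers are the outcome. No rule removes the item 8 drugs.

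**The concern.** A disorder that suppresses immunity may confound the association between eczema and cancer. A systemic drug given for eczema follows from the exposure and marks its severity. Item 10 gives both the same value of one variable and estimates one coefficient for them.

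If the hazard ratio falls in Table 10, the table does not show whether the cause is underlying immune disease or a second adjustment for eczema treatment. The distinction matters because dependence on systemic immunosuppressive treatment is a stated secondary aim. Item 8 says that the study is probably too small to examine effect modification by such treatment, so the adjustment tables carry most of the evidence on it. The plan does not mention the overlap between the two covariates and does not say how a change in Table 10 should be read.

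**Working it through.** The protocol gives no figure on this point, so there is none to reproduce.

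**Step 1: code overlap.** The systemic treatment codes come from Exposure subgroups, leaving out the four phototherapy codes (BNGA1 to BNGA4). Each is checked against the item 10 stems.

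| Item 10 stem | Systemic eczema codes covered |
|---|---|
| L04 | L04AX01, L04AX03, L04AD01, L04AA06 |
| L01 | L01BA01 |
| BOHJ | BOHJ18B8, BOHJ20, BOHJ22 |
| BWHB | BWHB83 |
| none | D11AH05, BWHA115 |

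Covered: 4 + 1 + 3 + 1 = 9 of 11. BWHA115 is printed as BWAH115 elsewhere, and neither spelling falls under BWHB. The Table 3 row that defines the item 8 covariate is only partly legible in the text at hand. Of its 7 legible codes 5 are covered, and the same two codes fall outside. The five drug names match in both places, so the complete list was used.

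**Step 2: what one shared coefficient does.** The protocol gives no prevalences or rate ratios, so all of these are assumed. The true hazard ratio is set at 1.10, with 10 comparators per patient and drugs independent of disorders. Poisson models were fitted to the expected counts. Prevalences are eczema versus comparators.

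| Case | Drugs | Disorders | What raises risk | Crude | Item 8 | Item 10 | Disorders alone |
|---|---|---|---|---|---|---|---|
| 1 | 8% v 1% | 1% v 1% | drugs, x2 | 1.18 | 1.10 | 1.13 | 1.18 |
| 2 | 1% v 1% | 8% v 1% | disorders, x2 | 1.18 | 1.18 | 1.13 | 1.10 |
| 3 | 8% v 1.5% | 2% v 1% | disorders, x2 | 1.11 | 1.11 | 1.08 | 1.10 |
| 4 | 8% v 1.5% | 2% v 1% | disorders, x5 | 1.14 | 1.14 | 1.04 | 1.10 |
| 5 | 3% v 1.5% | 1.5% v 1% | disorders, x5 | 1.12 | 1.12 | 1.09 | 1.10 |

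Entering drugs and disorders as two indicators returns 1.10 in all five cases. If drugs and disorders both double the risk, the single term also returns about 1.10, but nothing in the plan supports equal effects.

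**Step 3: hand check of case 4.** The crude value is 1.10 x (1 + 0.02 x 4) / (1 + 0.01 x 4) = 1.10 x 1.08 / 1.04 = 1.14.

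- Covariate on, eczema: 1 - 0.98 x 0.92 = 0.0984. Of these 0.02 / 0.0984 = 0.203 have a disorder, so the mean rate ratio is 1 + 4 x 0.203 = 1.81.
- Covariate on, comparators: 1 - 0.99 x 0.985 = 0.02485. Of these 0.01 / 0.02485 = 0.402 have a disorder, so the mean is 1 + 4 x 0.402 = 2.61.
- Hazard ratio within the covariate-on group: 1.10 x 1.81 / 2.61 = 0.76. In the covariate-off group it is 1.10.

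A Mantel-Haenszel combination of the two groups gives (0.908 + 0.141) / (0.825 + 0.184) = 1.04, which agrees with the model. The composite overshoots because eczema patients in the covariate-on group are mostly drug users, who carry no extra risk in this case. In case 2 the mix runs the other way. The covariate-on hazard ratio is 1.10 x 1.897 / 1.503 = 1.39, and the combined value is 1.13, so item 10 removes too little.

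**Step 4: reading the two tables together.** Cases 1 and 2 give the same Table 10 value of 1.13 and differ only in Table 8 (1.10 and 1.18), so the pair points to the right source. In cases 3 to 5 Table 8 does not move and Table 10 does. That shows the cause lies outside the item 8 drugs, but the size of the move is wrong. The same pattern could also come from other L01 or L04 drugs rather than disorders.

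**The case against.** The protocol openly labels item 10 as covering disorders or drugs. It never says that the item isolates disorders, or that Tables 8 and 10 are independent checks. That stands: this is a choice that limits interpretation, and the plan does not contradict itself here.

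A reader might infer that item 10 only repeats item 8 and cannot show whether immunosuppressive disorders confound. The documents do not support that. The composite is wider than item 8: it holds all of L01 and L04, HIV, transplant, immunodeficiency and haematological codes. An unchanged hazard ratio in Table 10 would argue against material confounding by disorders, unless opposing effects cancel. The two tables together also separate the single-cause cases.

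A reader might also treat every drug record as a consequence of eczema. The code lists carry no indication, so they capture the same drugs given for other diseases, and such use could confound. Disorders are time-updated too, so those arising after the index date are not clean baseline confounders.

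The count of 9 in 11 refers to codes. The protocol does not give the share of patients or person-time in the composite that is eczema treatment, and any such share would rest on assumed prevalences. Only one sensitivity analysis is affected.

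What remains is the shared coefficient. Comparing tables cannot repair the size of the item 10 estimate, and the plan gives no rule for reading it.

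**Conclusion.** The point holds in a limited form. The code overlap is established from the protocol: 9 of 11 systemic eczema codes lie inside the item 10 covariate, assuming that the partly legible Table 3 row holds the same drugs as the severity list. It follows that Table 10 on its own cannot attribute a change in hazard ratio to disorders rather than to eczema treatment.

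The size of any distortion is not known. With a true hazard ratio of 1.10, the illustration gives item 10 values from 1.04 to 1.13 for disorders-only effects, but every prevalence and rate ratio behind that range is an assumption. It shows that error in both directions is possible and does not predict which will occur. The primary models do not use this variable and are unaffected. The change is worth making because it uses codes already listed and bears on a named secondary aim.

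**What to change.** In Table 3 under Covariables, split the immunosuppression row in two:

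- (a) immunosuppressive disorders and transplant codes, without the lymphoma, myeloma and leukaemia codes when any cancer is the outcome. Prior cancer is excluded and follow-up ends at the first cancer, so in that analysis those codes would largely mark the outcome itself.
- (b) immunosuppressive drugs and procedures.

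Assign each procedure stem (BOQE, BOQF, BOHJ, BWG, BWHB) explicitly to (a) or (b).

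In Table 10, report the model with (a) alone and then the model with (a) and (b) as separate indicators. Add a sentence saying that the second model overlaps with item 8, and that drug use may follow from eczema or reflect other indications, so its change in hazard ratio is not read as confounding alone.

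The cost is one recode, one extra column, and a disorders-only term that will be rare and imprecise.

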## Analysis plan

|                       |       |                                                                                                                                                                                                                                      |                                                                                                                |
|-----------------------|-------|--------------------------------------------------------------------------------------------------------------------------------------------------------------------------------------------------------------------------------------|----------------------------------------------------------------------------------------------------------------|
|                       |       | "DC79" "DC80"
"DC81" "DC82"
"DC83" "DC84"
"DC85" "DC88"
"DC90" "DC96"
"DC91" "DC92"
"DC93" "DC94"
"DC95" except codes
for cutaneous
lymphoma ("C826"
"C840" "C841" "C848"
"C863" "C866"
"C884B") |                                                                                                                |
| Lung           |       | "C34"                                                                                                                                                                                                                                |                                                                                                                |
| Breast         |       | "C50"                                                                                                                                                                                                                                |                                                                                                                |
| Prostate       |       | "C61"                                                                                                                                                                                                                                |                                                                                                                |

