### Follow-up

- Follow-up start: index date.
- Follow-up end: earliest of emigration, death, end of study (30 June 2017) or first-ever cancer diagnosis (when examining specific cancers, patients are thus censored if diagnosed with another individual cancer).
- If a person from the comparison cohort is diagnosed with eczema during follow-up, that person will be censored at time of diagnosis. The person will then contribute to the eczema cohort together with his/her own comparators (this has been accounted for in the sampling done by the Danish Health Data Authority)

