## Analysis plan

3. With time since index date as underlying time scale, we will use stratified Cox regression (conditioning on matched set) to compute unadjusted hazard ratios (99% confidence intervals) to determine associations between eczema and each outcome (that is, comparing eczema patients and the comparison cohort). By stratifying on matched set, the model accounts for birth year, sex and calendar period. We will then fit a “mediation model” additionally adjusting for time-varying lifestyle-related diseases (chronic obstructive pulmonary disease, hyperlipidemia, hypertension, alcohol-related conditions, ischemic heart disease, hospital-diagnosed obesity and type II diabetes). If sufficient power, we will adjust for the lifestyle-related diseases as individual variables.

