Unadjusted: Adjusted additionally for **immunosuppression**.

Mediation model: Adjusted additionally for time-varying lifestyle-related diseases **and immunosuppression**.

11. We will repeat the main analysis additionally adjusting for use of **oral corticosteroids**. We will define use as a time-updated never/ever variable. Thus, individuals classified as exposed if they ever have a prescription for an oral corticosteroid, with status changing at the first prescription for an oral corticosteroid.

---

**Table 11. Number of events, accumulated person-time, and HRs for cancer associated with eczema, Denmark. Adjusting additionally for oral glucocorticoids.**

---

| N | events | P-Y
at
risk | Rate
per
1,000 | Hazard ratio and 99%
confidence interval  |                    |
|---|--------|-------------------|----------------------|----------------------------------------------------------|--------------------|
|   |        |                   |                      | ‘Unadjusted’                                             | Mediation
model |

---

---

|                                  |
|----------------------------------|
| Any cancer                       |
| Unexposed                        |
| Exposed                          |
| Lung cancer                      |
| Unexposed                        |
| Exposed                          |
| Breast cancer                    |
| Unexposed                        |
| Exposed                          |
| Prostate cancer                  |
| Unexposed                        |
| Exposed                          |
| Melanoma skin cancer             |
| Unexposed                        |
| Exposed                          |
| Keratinocyte skin cancer         |
| Unexposed                        |
| Exposed                          |
| Lymphoma                         |
| Unexposed                        |
| Exposed                          |
| Multiple myeloma                 |
| Unexposed                        |
| Exposed                          |
| Leukemia                         |
| Unexposed                        |
| Exposed                          |
| Meningioma                       |
| Unexposed                        |
| Exposed                          |
| Cancer of the brain, hypophysis, |
| corpus pineale and ductus        |
| craniopharyngealis               |
| Unexposed                        |
| Exposed                          |

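### In sensitivity analysis 10 (Table 10), the any-cancer row is adjusted for an immunosuppression variable that still contains lymphoma, myeloma and leukaemia codes, so the outcome itself can switch the covariate on

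*Protocol*

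**What the plan says.** **The covariate.** The covariables table (Table 3, Immunosuppression row) lists ICD-8 200–207 and ICD-10 DC81–DC86, DC88 and DC90–DC96, beside other disorders, drugs and procedures. The note on that row reads "Exclude codes for myeloma, lymphoma and leukemia respectively from code list for the" variable, and it applies when these cancers are the outcome. No rule is given for a composite outcome that contains them.

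**Its timing.** Apart from socioeconomic status, covariables are time-updated and stay on once set. The table footnote says "Use admission/prescription/record date for all variables".

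**Where it is used.** Sensitivity analysis 10 says "We will repeat the main analysis additionally adjusting for immunosuppression (immunosuppressive disorders or drugs". The first row of Table 10 is any cancer. Both columns carry the covariate, since the first is footnoted "Unadjusted: Adjusted additionally for immunosuppression".

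**Outcome and follow-up.** Outcomes come from the Danish Cancer Registry. People with a cancer record on or before the index date (other than non-melanoma skin cancer) are excluded, and follow-up ends at "first-ever cancer diagnosis" if nothing else ends it sooner.

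**The concern.** The note in Table 3 exists because a model should not adjust for its own outcome. The same reasoning applies to any composite that includes lymphoma, myeloma and leukaemia, yet the rule stops at the cancer-specific analyses. In the any-cancer row the haematological codes remain in the covariate.

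Those codes can hardly represent pre-existing immunosuppression, because people with earlier cancer are not in the cohort and nobody is followed past a first cancer. What remains is mostly the hospital record of the incident cancer. If that record is dated at an admission before the Cancer Registry date, the case enters its own risk set with the covariate on, while its matched comparators almost all have it off.

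At stake is how Table 10 is read. A fall in the eczema hazard ratio after adjustment would naturally be taken to mean that immunosuppression accounts for the association. Here a fall could arise from the code list alone.

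**Working it through.** The plan states no figure on this point, so there is nothing to reproduce. The check has three parts.

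**1. Code overlap (from the documents).**
- Covariate, haematological ICD-10: DC81, 82, 83, 84, 85, 86, 88, 90, 91, 92, 93, 94, 95, 96, which is 14 codes.
- Any-cancer outcome (Table 2, Cancer outcomes): DC81–DC85, DC88 and DC90–DC96, minus cutaneous lymphoma subcodes.
- Common to both: 13 of 14. Only DC86 is missing from the outcome.
- The eight ICD-8 numbers 200–207 also appear in the outcome's ICD-7 list. This is a match of code numbers only, as the classifications differ.

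**2. How the bias arises.** In a set of one eczema patient and ten comparators, the conditional Cox likelihood contribution is exp(βE + γX) for the case, divided by the sum of the same term over the set. E is eczema and X is immunosuppression.

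- *Events that set their own covariate.* Take eczema HR 1 and no other immunosuppression in the set. An eczema case contributes 1 − HRx/(HRx + 10) to the score for β, and a comparator case contributes −1/(HRx + 10). At HRx = 1 these are 0.909 and −0.091. At HRx = 6 they are 0.625 and −0.0625. Such events are down-weighted by 11/16 = 0.69. They do not lose all their information.
- *All other events.* The inflated covariate HR is applied to genuine immunosuppression. Assume prevalence 6% in eczema and 2% in comparators, with a true covariate HR of 1.5. The correct weight ratio is (1 + 0.06×0.5)/(1 + 0.02×0.5) = 1.020. With a covariate HR of 3.88 it becomes (1 + 0.06×2.88)/(1 + 0.02×2.88) = 1.109. The eczema HR has to absorb 1.020/1.109 = 0.92.

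**3. Illustrative simulation (all inputs assumed).** Each scenario had 300,000 sets of 1 + 10, one event per set and a true covariate HR of 1.5. Prevalence (eczema/comparators) was 3%/1%, 6%/2% or 10%/2%. A share q of all events had the case's covariate switched on by the outcome. Here q = (haematological share of cancers) × (share of those with the hospital record dated first). With an assumed 10% haematological share, q = 2%, 5% and 10% correspond to 20%, 50% and 100% coded first.

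| q | Eczema HR, true 1.0 | Eczema HR, true 1.1 | Covariate HR (eczema HR 1.0; true 1.5) |
|---|---|---|---|
| 0 | 1.00–1.01 | 1.09–1.10 | 1.5 |
| 2% | 0.95–0.98 | 1.05–1.07 | 2.3–3.3 |
| 5% | 0.89–0.95 | 0.98–1.04 | 3.7–6.2 |
| 10% | 0.81–0.92 | 0.90–1.00 | 6.0–11.4 |

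At prevalence 6%/2% and q = 5% the simulated eczema HR was 0.933 with covariate HR 3.88, close to the hand figure of 0.92.

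A second set of assumptions used a 10% haematological share, eczema HR 1.5 for those cancers, covariate HR 1.3 and prevalence 3%/1% or 6%/2%. With 50% coded first it gave 1.04–1.06 correctly adjusted against 0.97–0.99 as written. With 10% coded first it gave 1.04–1.05 against 1.02–1.03.

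**The case against.** - **The note may already cover composites.** It ends with one pooled list of codes, and any cancer can be described as an outcome that includes these cancers. The wording is strained by its one-to-one assignment of codes to named cancers, and two programmers could produce different any-cancer rows. The text needs settling on either reading.
- **The timing is not documented.** This stands. The plan gives no relative dates for the two registries and no rule for ties. If a covariate change takes effect only after its date, same-day records do no harm, and with no early coding there is no shift (q = 0 above). That convention does not protect against an admission dated before the Cancer Registry date.
- **The size is unknown.** This also stands. Every simulation input is assumed and the two sets of inputs give different sizes. With no event counts in the plan, the shift cannot be set against a 99% confidence interval.
- **The main any-cancer result.** A reader might infer that it is over-adjusted. It is not: the models in item 3 are the unadjusted one and the one "additionally adjusting for time-varying lifestyle-related diseases", and neither contains immunosuppression.
- **The covariate's own hazard ratio.** A reader might expect a distorted value to be published. The Table 10 shell has rows only for unexposed and exposed, so it is not a planned output.
- **Drug and procedure codes.** A reader might think these must be lagged as well. Treatment after the registered diagnosis falls outside follow-up. Only treatment dated before registration could matter, and the documents do not show how common that is.

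**Conclusion.** The point holds for the any-cancer row of Table 10, in both columns, and for any overall haematological estimate adjusted in the same way. As written, the covariate includes diagnoses that belong to those outcomes, and cohort entry and follow-up rules leave such codes little other meaning. The small exceptions are DC86 and the cutaneous lymphoma subcodes, which are in the covariate but not in the any-cancer outcome.

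The bias needs some hospital records to predate the Cancer Registry date. It was downward in every scenario tried, but all of these assumed that immunosuppression is commoner in eczema patients. Without that, or if eczema had a weaker effect on haematological than on other cancers, the direction would not be assured. The size cannot be determined from the documents. The figures above show only that a few per cent of self-coded events can move a hazard ratio near 1 by several hundredths or more. The error is confined to one sensitivity analysis and leaves the primary results untouched. It still deserves correction before analysis, because the distortion resembles a substantive finding.

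**What to change.** Extend the note in the Immunosuppression row of Table 3. When the outcome is any cancer or overall haematological cancer, all the listed codes (ICD-8 200–207; ICD-10 DC81–DC86, DC88, DC90–DC96) are removed from the variable, including where they serve as the A-diagnoses that qualify DZ948.

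This is one sentence and one code-list change for these outcomes. Little valid exposure is lost, since prior cancer is already excluded and a first cancer ends follow-up. The loss is limited mainly to DC86 and cutaneous lymphoma codes in the any-cancer row.

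A lag before drug and procedure codes switch the variable on could be run as an optional further check. It is not part of the correction, and it would delay some genuine exposure time.
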